### Ethics

This study will be carried out in conformity with the study protocol and the Declaration of Helsinki. Furthermore, it will guarantee the confidentiality and security of the data following the guidelines set forth in the current laws and data protection regulations: The General Data Protection Regulation, agreed upon by the European Parliament and Council in April 2016. Moreover, all important EU legislation and international documents on privacy will be followed.

All participants will be volunteers. When the study has been explained to them, they will sign the online informed consent to participate. Qualified clinical personnel will conduct the clinical assessment of the participants as part as the recruitment process. In the same way, all the tasks involving the participants will be performed by qualified, expert professionals (Clinical Psychology PhD). The assessment protocol is composed of standardized instruments (semi-structured interviews and questionnaires). Likewise, treatment protocols are based on empirically-validated treatments from the Task Force on the Promotion and Dissemination of Psychological Procedures of the American Psychological Association [60].

Data protection is an important aspect of the project. To access the Internet platform, the participants will have a unique username and password combination. Furthermore, the platform will be available on a 24/7 basis. Moreover, the transferred data will be secured using AES encryption (AES-256; Advanced Encryption Standard).

The study policies do not differ from those used in other clinical trials focused on the treatment of depression through the Internet, and so no special difficulties are expected.

The study has been approved by the Ethics Committee of University Jaume I (Castellon, Spain, approval number: 4/2017). The trial is registered at clinicalstrials.gov as NCT03159715.

Important protocol modifications will be communicated to relevant parties (i.e., trial participants, trial registries, journals, ethical committee and researchers).

### Interventions

#### Internet-based global protocol condition (IGc)

We have developed a manualized intervention protocol for depressive symptoms called Sonreír es Divertido (Smiling is Fun in English). It is an Internet-based program developed in a European project: Online predictive tools for intervention in mental illness [51]. Smiling is Fun includes the psychological treatment components that are traditionally incorporated in evidence-based interventions for depression: Motivation for change, Psychoeducation, Cognitive Therapy, BA, and Relapse Prevention. The program also incorporates a PPs component, offering tools to improve positive affect and promote strengths.

The intervention program includes eight modules: four CBT based modules; three PPs based modules, and one Relapse prevention module.

Regarding the CBT modules: 1) “*Motivation for change*”, 2) “*Understanding emotional problems*”, 3) “*Learning to move on*”, and 4) “*Learning to be flexible*”, their main objectives, respectively, are: a) To analyze both the advantages and disadvantages of changing their behaviors, feelings, and thoughts; b) To offer information to help the patient to understand the characteristics of the emotional problems; c) To explain the importance of being involved in life and acquiring an appropriate activity level; and d) To teach the patients how to think in a more flexible manner.

In the case of the PPs modules, designed to promote positive affect, well-being, and psychological strengths: 5) “*Learning to enjoy*”, 6) “*Learning to live*”, 7) “*Living and learning*”, their principal objectives are, respectively: a) To “savor” and enjoy positive life experiences; b) To do activities linked to their own goals and values and learn how to identify their psychological strengths; c) To know how to improve their psychological strengths and start working toward the future.

At the end of the program, there is a Relapse prevention component in module 8) “*From now on, what else…*?”, whose objectives are: a) To review what has been learned in each module; b) To learn that finishing the program does not mean no longer practicing the strategies learned, and that it is the beginning of each patient’s path; and d) To invite them to think about what they would like their future life to be like.

#### Internet-based BA protocol condition (IBAc)

This intervention protocol has these CBT components from the original protocol (*IGc*) explained above: Motivation for change, Psychoeducation, Cognitive Flexibility, BA, and Relapse Prevention. The PPs component is not included in this protocol.

The BA component in this protocol teaches the same things as the BA component in *IGc.*

#### Internet-based PPs protocol condition (IPPc)

This intervention protocol has these CBT components from the original protocol (*IGc*) explained above: Motivation for change, Psychoeducation, Cognitive Flexibility, and Relapse Prevention. The BA component is not included in this protocol.

The PPs component in this protocol teaches the same things as the PPs component in *IGc.*

Table 1 showed the structure of the IBAc and IPPc.

**Table 1 Tab1:** The structure of the IBAc and IPPc

Internet-based BA Protocol condition (IBAc)	Internet-based PPs Protocol condition (IPPc)
Modules/ Therapeutic component	Modules/ Therapeutic component
1.“Motivation for change”/ Motivation	1.“Motivation for change”/ Motivation
2.“Understanding emotional problems”/ Psychoeducation	2.“Understanding emotional problems”/ Psychoeducation
3.“Learning to be flexible”/ Cognitive Flexibility	3.“Learning to be flexible” / Cognitive Flexibility
4.“Learning to be active”/ BA	4.“Getting involved with life”/ PPs
5.“My significant activities”/ BA	5.“Enjoying life”/ PPs
6.“Seeking support to be active”/ BA	6.“Accepting life”/ PPs
7.“Keeping my life active”/ BA	7.“Achieving a full life”/ PPs
8.“From now on, what else…?”/Relapse prevention	8.“From now on, what else…?”/Relapse prevention

Note. Modules 1, 2, 3, and 8 are included in all three conditions

It is important to mention that the three protocols have the same number of modules (eight) and a similar number of words: IGc: 35.123; IBAc 35.492 and IPPc: 39.002 (M: 36541; SD: 2139.003).

The three treatment protocols include a “Welcome” module that explains information about the treatment protocol and its purposes. Furthermore, it explains the main recommendations for obtaining the most benefit from it. After this “Welcome” module, the patients access the pre-treatment assessment online questionnaires. After the pre-treatment assessment, participants start the intervention modules. Table 2 shows the structure of each module. The modules include exercises to practice each technique and skill. Furthermore, at the end of each module, there is a post-module assessment to evaluate depression, anxiety, and positive/negative affect. When participants complete the eight treatment modules, they perform the post-treatment assessment, which is also integrated in the web system (the same self-report questionnaires as in the pre-treatment assessment, plus the treatment satisfaction scale).

**Table 2 Tab2:** Structure of each module

Structure of each module	
1. Questions related to the previous module	
2. Specific contents of the module	
3. Exercises related to the content of the module	
4. Homework tasks telling them to work on what was presented in the module	
5. Post module assessment: depression, anxiety, positive and negative affect	

An important function of the program is that the therapists have access to all the information participants provide during the treatment, so that if the patient’s condition gets worse they can receive an alert. These alerts are generated by the system when a high risk of suicide is detected. Then, an email is sent to the clinical team so that the therapist can contact the patients and make better decisions to protect and help them.

Regarding the use of the intervention, participants will progress sequentially through the program at their own rhythm, but they will be informed that they will receive the most benefit from the intervention if they do about one module every 2 weeks. This is the time stipulated to complete each module and practice the techniques and strategies learned. The participants will be informed that they have a maximum of 16 weeks to complete all eight modules. As the intervention progresses, when they finish one module, they will be allowed to look it over again if they so desire.

All the modules will be on a web platform developed by our research group (https://www.psicologiaytecnologia.com/). It was designed for optimal use on a tablet or a PC and to optimize the understanding of the modules’ content using different multimedia elements such as audio, vignettes, video, etc. The web platform has different transversal tools that accompany the person throughout the entire intervention process (Table 3).

**Table 3 Tab3:** Transversal tools of the web platform

“Home”	This tool is the starting point of the protocol, appears on the main menu, and is used to access the other sections of the protocol. It also shows the progress through the treatment.
“Calendar”	In this section, the participant can know where he/she is in the program. This tool also shows the days on which the participant has accessed the program, as well as both pending and achieved tasks.
“Review”	This section is used by participants to review the treatment modules already completed. This tool allows them to have access to the different modules as often as they wish.
“How am I”	This section offers several graphs that make it possible to monitor the participant’s progress. It provides feedback to participants about their activity level, emotional distress, and positive and negative emotionality.
“Diary register”	The objective of the “Diary register” is to collect data every day about different variables (activity level, emotional distress, positive and negative emotionality) and show them graphically on the “How am I” tool.

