If the participants fulfill the eligibility criteria, they will be randomized to one of the three experimental conditions by an independent investigator who will not have information about the RCT’s characteristics. Randomization will be performed using a weighted random number sequence generated by a computer, in order to have a homogeneous distribution across the three conditions. The study researchers will be informed about the allocation schedule via telephone call. Before the allocation to one of the three interventions, the patients will agree to participate without having the information about which intervention they will be receive. Nevertheless, for pragmatic reasons, researchers and patients will not be blind to the intervention conditions. At any time during the study, the participants will be allowed to drop out of the intervention without giving any reasons.

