### Support

In the intervention conditions, the participants will receive human and ICT support.

Regarding human support, one trained predoctoral student in our group will make several brief phone calls at four points in time:*An initial telephone session:* to explain the characteristics of the RCT to the participant and administer the clinical diagnostic interview and find out whether s/he fulfills the inclusion criteria.*An initial phone call in the “Welcome” module*: encouraging patients to start the program, do one module every 2 weeks, and do the homework tasks in each module. This phone call will take place when the participants do the pre-treatment assessments.*One brief phone call (maximum of 10 min) when the participants reach the mid-point of the intervention (module 4)*: 1) to ask the participants about any doubts or difficulties regarding the use of the program and help them; 2) to remind them that they can review the content of each module; 3) to emphasize the importance of doing the tasks in each module and practice the strategies they learn; 4) to motivate patients to continue with the program and positively reinforce them for engaging in the intervention; and 5) to remember that the best way to experience the intervention is by doing one module every 2 weeks.*A final phone call after the post-assessment:* to ask them their qualitative opinion about the intervention and remind participants that they will be allowed to use the intervention program any time they want to during the study period, and that we will contact them to do the follow-up assessment.

ICT support will consist of multiple-choice questions about the module’s contents in order to provide the participant with the correct feedback for their responses and a detailed explanation. Furthermore, the participants will receive an automated email encouraging them to continue with the modules if they have not accessed the program for a week. In addition to this automated support, the program offers continued feedback to users through the transversal tools described earlier.

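### The online pre-treatment battery apparently follows randomisation and the Welcome module, so PANAS has no described pre-randomisation baseline and the BDI-II analysis baseline is not named.

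*Protocol article*

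**What the plan says.** **Allocation.** In Participants, recruitment and eligibility criteria: "If the participants fulfill the eligibility criteria, they will be randomized to one of the three experimental conditions". The same paragraph states that "researchers and patients will not be blind to the intervention conditions". Under Support, eligibility is settled in an initial telephone session that includes the diagnostic interview.

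**Pre-treatment battery.** The text after Table 1 says that each of the three protocols contains a Welcome "module that explains information about the treatment protocol and its purposes". After this "module, the patients access the pre-treatment assessment online questionnaires". Then: "After the pre-treatment assessment, participants start the intervention modules". Under Support, a call made during the Welcome module encourages participants to begin: "This phone call will take place when the participants do the pre-treatment assessments".

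**Use of the battery.** The post-treatment assessment repeats the same self-report questionnaires. Statistical analysis tests primary outcomes by repeated-measures ANOVA with main and interaction effects. Sample size and power calculations rests on the interaction of intervention and measurement occasion.

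**BDI-II before allocation.** Entry requires a BDI-II score of 14 to 28, and Study design stratifies randomisation by depression severity. Both need a score before randomisation. No sentence says whether that score or the online one is the analysis baseline. Table 4 does not settle it: its baseline column also lists the MINI, which belongs to the eligibility call.

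**The concern.** In a test of change, the baseline is one of the terms being compared. Randomisation makes the arms comparable in expectation on anything measured before allocation, but not on what is measured afterwards. Both primary outcomes are self-reported, and one of them measures affect. If knowing the assigned programme moves the pre-treatment score differently in different arms, that movement counts as a difference in change. It can create an interaction where there is none, or hide a real one.

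There is also a gap for the intention-to-treat analysis. A randomised participant who stops before the battery has no PANAS baseline. Because the modules start only after the battery, such a person is also unlikely to supply later values from which the baseline could be estimated.

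**Working it through.** **1. Order of events.** The article gives three links: eligible, then randomised; the Welcome module is part of each treatment protocol; the questionnaires follow the Welcome module. A participant needs an allocated protocol to reach its Welcome module, so the battery comes after randomisation. No sentence says this outright, and none contradicts it.

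**2. Which test was sized.** Inputs from Sample size and power calculations: explained variance 0.01, alpha 0.05, power 0.80, sphericity, correlation ρ = 0.7, three groups. The number of occasions m is not given. For the within-between interaction F test:

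- f² = 0.01/0.99 = 0.0101
- λ = f² × N × m/(1 − ρ), df1 = 2(m − 1), df2 = (N − 3)(m − 1)

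| m | Smallest N, equal arms | Power at that N |
|---|---|---|
| 2 | 147 | 0.803 |
| 3 | 123 | 0.809 |
| 4 | 105 | 0.808 |
| 5 | 93 | 0.809 |

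Only m = 2 gives the stated 147. The sized test is in effect pre versus post, with 'pre' as one of its two terms.

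**3. Planned effect in SD units.** With two occasions the interaction test equals a one-way ANOVA on post minus pre. The variance of that change is 2(1 − 0.7) = 0.6 SD².

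- λ = 0.0101 × 147 × 2/0.3 = 9.90
- With 49 per arm, λ = 49 × S/0.6, where S is the sum of squared deviations of the arm means; so S = 0.1212.
- If one arm differs from the other two by d, then S = (2/3)d², so d = √(1.5 × 0.1212) = 0.43 SD.

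**4. Effect of a shift at 'pre'.** The article gives no shift size, so these are assumptions. A shift s in one arm changes that arm's mean change by s. For s = 0.1, 0.1/0.426 = 23% of the planned difference; for s = 0.2, 47%. With no true effect on the post score, the rejection rate from the noncentral F with λ = n × (2/3)s²/0.6 is:

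| Assumed shift in one arm | 49 per arm | 64 per arm |
|---|---|---|
| 0 | 5.0% | 5.0% |
| 0.1 SD | 9.2% | 10.7% |
| 0.2 SD | 23.8% | 30.2% |
| 0.3 SD | 48.7% | 60.6% |

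Simulation at 49 per arm (6,000 runs per setting) gave 5.2%, 9.1%, 23.4% and 48.3%. With a pre-randomisation score as 'pre', the same simulation gave 4.9%, 4.9%, 4.9% and 5.4%.

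**5. Missing baselines.** If 5% to 10% of those randomised stop before the battery (an assumption), 0.05 × 192 = 9.6 and 0.10 × 192 = 19.2, so about 10 to 19 people would have no PANAS baseline.

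**The case against.** The strongest reply is that little can differ between arms this early. All three arms are active eight-module programmes of similar length, and there is no waiting list to disappoint anyone. The support calls are described once for all conditions. Only a differential shift matters; a lift that the Welcome module or the call gives to everyone cancels in the group-by-time contrast. This stands, and it is why the tables above show sensitivity rather than a forecast.

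The BDI-II also has a pre-randomisation value. That stands too: for this outcome the defect is that the baseline is not named, and it can be repaired for everyone. It does not help PANAS.

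The planned maximum likelihood handling of missing data is a partial answer at most. The article introduces it for outcomes at post-treatment and follow-up, and it does not change when the baseline is taken.

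Three stronger readings are tempting but not supported:

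- **That the Welcome module frames each arm differently.** The article does not say that its text varies by arm, nor when participants learn their arm; it says only that they are not blind.
- **That the encouraging call precedes the questionnaires.** It is described as taking place while they are completed.
- **That researchers see the whole allocation list in advance.** The sentence "The study researchers will be informed about the allocation schedule via telephone call" could suggest it, but this rests on one word that may be loose phrasing, and it is a separate matter from baseline timing.

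**Conclusion.** The point holds as a design weakness that should be corrected. Followed as written, the plan takes the PANAS 'pre' value after allocation in a trial where patients are not blind, and it leaves open which BDI-II score is 'pre'. Randomisation does not protect a term of the primary contrast for PANAS, and may not for the BDI-II.

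The 23% figure rests on an assumed 0.1 SD shift in one arm, two measurement occasions, ρ = 0.7, and one arm differing from the other two. The documents show a risk of bias, not its size or direction, and nothing in them shows that bias has occurred. A reader might infer that both primary outcomes lack a valid baseline. The entry criterion and the strata rule that out for the BDI-II. If the flowchart or the full protocol places the battery before allocation, one clarifying sentence resolves the timing.

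**What to change.** **Participants not yet randomised.** Open the pre-treatment battery after consent and confirmed eligibility. Release the allocation and the Welcome module only once the platform shows the battery as complete. Study design says that recruitment is under way, so this can still help those yet to enter.

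**Participants already randomised.** Name the eligibility BDI-II as the BDI-II baseline. State that their PANAS baseline was taken after allocation. Add a sensitivity analysis that compares arms on post-treatment PANAS without the 'pre' value.

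**Cost.** One platform step and a few sentences. Allocation waits for the questionnaires. Baseline timing will differ before and after the change, which should be reported. The post-only PANAS comparison is less precise: at ρ = 0.7 its variance is 1 SD² per person against 0.6 SD² for change, so standard errors are √(1/0.6) = 1.29 times as large. It therefore serves as a check rather than a replacement.

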### Statistical analysis

Per protocol and Intention-to-treat (ITT) analyses will be performed, following the CONSORT and CONSORT-eHealth recommendations [56, 83]. Between-group differences in baseline clinical and socio-demographic characteristics will be explored using analysis of variance (ANOVA) for continuous data, and chi-square tests (χ2) for categorical variables. Both normality and multinormality assumptions will be assessed by applying the Kolmogorov-Smirnov (K-S) test, skewness and kurtosis indexes, and histogram and Q-Q plots. Levene’s test will be conducted to check homoscedasticity assumptions for equality of variances, and Mauchly’s test to explore sphericity assumptions. Missing data patterns will be assessed, and whether missing data are missing completely at random (MCAR) will be checked with Little’s MCAR test [84]. The ITT principle will be applied for primary and secondary outcomes collected at post-treatment, and at the 3, 6, and 12-month follow-ups. In this regard, the maximum likelihood (ML) method using the Expectation Maximization (EM) algorithm will be used to deal with missing data, due to its flexibility in repeated-measures ANOVAs in handling missing data appropriately (i.e., [85, 86]. Nevertheless, several approaches will also be considered and assessed using sensitivity analyses in order to apply the most robust and adequate method based on both missing data patterns and literature recommendations (i.e., [87, 88]. Repeated analysis of variance (rm-ANOVA) will be performed to explore the main and interaction effects of the treatments on all the primary and secondary outcomes. Significant effects will be followed up by pairwise comparisons, such as the Tukey procedure when the homoscedasticity assumption is met, and the Games-Howell procedure if this assumption is not met. Effect sizes (Cohen’s *d*) and their respective 95% confidence intervals (95% IC) will be calculated and reported for within- and between-group comparisons, according to authors’ recommendations [89–91]. In addition to ITT analyses, per protocol analyses will also be conducted. It is true that these analyses suffer from selection bias, but they will allow us to reach conclusions about the efficacy of the treatment in patients who complete all the intervention modules [92].

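### Post-treatment assessment is triggered by finishing all eight modules, with no stated route for non-completers, so post-treatment BDI-II goes missing in step with adherence

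*Protocol article*

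**What the plan says.** All references are to the protocol article.

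- **Trigger.** The Interventions section (text after Table 1, under the IPPc heading) states: "When participants complete the eight treatment modules, they perform the post-treatment assessment, which is also integrated in the web system".
- **Pace.** In the same section, "participants will progress sequentially through the program at their own rhythm". The advice is about one module per two weeks, and participants are told that "they have a maximum of 16 weeks to complete all eight modules". No assessment is attached to the end of that period.
- **Stopping.** Under Participants, recruitment and eligibility criteria, "the participants will be allowed to drop out of the intervention without giving any reasons". This concerns leaving the intervention. Nothing is said there about assessing those who leave it.
- **Measures during treatment.** "at the end of each module, there is a post-module assessment to evaluate depression, anxiety, and positive/negative affect". In Table 4 these are PANAS, ODSIS and OASIS. BDI-II is scheduled only at baseline, post-treatment and the 3-, 6- and 12-month follow-ups.
- **Contact.** In the Support section, the call that tells participants they will be contacted for follow-up is described as "A final phone call after the post-assessment". The automated e-mail after a week without access encourages people to continue with the modules.
- **Analysis.** "The ITT principle will be applied for primary and secondary outcomes collected at post-treatment, and at the 3, 6, and 12-month follow-ups", and "the maximum likelihood (ML) method using the Expectation Maximization (EM) algorithm will be used to deal with missing data". Per-protocol analyses concern patients who finish all modules, and the section concedes that such analyses carry selection bias.

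**The concern.** The analysis section promises intention-to-treat at post-treatment, while the stated timing rule ties the measurement to adherence. Stopping treatment and having no post-treatment BDI-II become, as written, the same event. Whether someone finishes eight modules plausibly depends on how they are responding and on how acceptable the version they received is, and acceptability is itself a study objective. A comparison of three active arms could then partly reflect who finished.

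Timing is a second, smaller issue. The Discussion says all patients get the same amount of time as a way of offsetting the unequal number of BA and PPs modules across arms. If the outcome is taken at completion, elapsed time follows pace and that offset is weakened.

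Outcomes that were not collected cannot be recovered at analysis. The article describes the trial as still recruiting, so the point is best settled in the protocol.

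**Working it through.** **1. Who has what, as written**

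| Participant | Post-treatment BDI-II | PANAS and ODSIS | Per-protocol set |
|---|---|---|---|
| Finishes eight modules | yes | after every module and at post-treatment | yes |
| Stops after module k < 8 | no route described | up to module k | no |
| Unfinished at 16 weeks | no route described | up to last module completed | no |

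The advised pace leaves no slack: 8 modules × 2 weeks = 16 weeks, so anyone slower than advised is unfinished at the limit. The first and last columns show that the observed post-treatment BDI-II set essentially coincides with the per-protocol set.

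**2. Reproducing the planned sample size**

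Inputs from Sample size and power calculations: explained variance 0.01, alpha 0.05, power 0.80, sphericity, correlation 0.7, three arms. The number of occasions m is not stated.

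- f² = 0.01/0.99 = 0.0101
- λ = f² × N × m/(1 − ρ), with df1 = (3 − 1)(m − 1) and df2 = (N − 3)(m − 1)
- m = 2, N = 147: λ = 0.0101 × 147 × 2/0.3 = 9.90, power 0.803. This matches the stated 147. With m = 3, 4 or 5 the required N would be 123, 105 or 93, so m = 2 is inferred.
- Dropout allowance: 147 × 1.3 = 191.1, taken to 192 (64 per arm). This also matches.

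**3. Post-treatment BDI-II values at risk**

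Assumption: the 30% dropout is module non-completion. The article does not say whether it means dropout from treatment or from assessment.

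| Non-completion | Missing of 192 | Observed |
|---|---|---|
| 20% | 38.4 | 153.6, about 154 |
| 30% | 57.6, about 58 | 134.4, about 134 (about 45 per arm) |
| 40% | 76.8 | 115.2, about 115 |

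At N = 134, λ = 0.0101 × 134 × 2/0.3 = 9.02 and power is about 0.76. The 147 is kept only if non-completion is at most (192 − 147)/192 = 23.4%. This shortfall at 30% would follow from any 30% loss, because the allowance multiplies by 1.3 and does not divide by 0.7 (147/0.7 = 210). What the trigger adds is that the loss is selective.

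**4. Between-arm bias**

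Let c be the completion proportion in an arm, and Δ the amount in SD by which non-completers' true scores are worse than the missing-at-random prediction. The arm mean is then too favourable by (1 − c)Δ. For two arms with a common Δ:

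bias = [(1 − c₂) − (1 − c₁)] × Δ

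- Equal completion: 0, whatever Δ is.
- Assumed 80% versus 60%: (0.40 − 0.20)Δ = 0.20Δ, which is 0.10 SD at Δ = 0.5 and 0.20 SD at Δ = 1.0. It favours the arm with lower completion.

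If Δ itself differed between arms, equal completion would not guarantee zero. The documents give no value for c by arm or for Δ.

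**The case against.** The text says when completers are assessed and is silent about everyone else. That nobody else is assessed is an inference from a condensed article, and the procedure for pursuing non-completers may well be in the full protocol. The article also plans intention-to-treat and per-protocol analyses separately, which suggests the authors did not regard the two sets as identical. This stands, and it is why the point is worded as written. It does not dispose of the point, because the article does state a timing rule and that rule depends on adherence.

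A reader might infer that non-completers have no primary outcome at all, or that intention-to-treat is impossible. The documents do not support either:

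- PANAS is also a primary outcome and is collected after each module, as is ODSIS. Someone who stops at module 5 contributes several scores, though none after that.
- Table 4 schedules BDI-II at 3, 6 and 12 months without a completion condition. If obtained from non-completers, those values give indirect evidence about them.
- All randomised participants can be analysed by likelihood methods, and sensitivity analyses are promised.
- No passage ranks post-treatment above the follow-ups as the primary time point.

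The bias range is also open to challenge. All arms have eight modules, similar word counts, the same time limit and the same support, so a 20-point completion gap is only an assumption. With the protocol's correlation of 0.7, the residual SD given baseline is √(1 − 0.49) = 0.71, so Δ = 1.0 is about 1.4 residual SDs, which is large.

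Finally, measuring at the end of a self-paced treatment is a legitimate choice, and the variation in timing is bounded by 16 weeks in every arm. That tempers the timing issue. It does not address the missing values.

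**Conclusion.** The point holds in a limited form: it concerns BDI-II at the post-treatment visit. Under the rule as written, that value is missing in step with adherence, its observed set is essentially the per-protocol set, and the intention-to-treat result there depends on a missing-at-random assumption that cannot be tested without post-treatment data from people who stopped. Little's test, which is planned, addresses only missingness completely at random. Assessment time also varies with pace.

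The size depends on reading the 30% as module non-completion: about 58 of 192 values missing, 134 observed against 147, and power about 0.76, with about 154 observed at 20% and about 115 at 40%. Bias ranges from zero, with equal completion and a common Δ, to 0.10–0.20 SD under the assumed 80% versus 60% completion and Δ of 0.5 to 1.0 SD. These bias figures are illustrations, not estimates. The stronger conclusions, that intention-to-treat cannot be done or that non-completers contribute no primary outcome data, should not be drawn.

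**What to change.** State in the protocol that the post-treatment battery is offered to every randomised participant at a fixed time after allocation, using the existing 16-week limit, whatever number of modules has been completed. Use the automated e-mail and the phone contact already in place, and say how those who have stopped the programme are reached. Date the 3-, 6- and 12-month follow-ups from that same point for everyone. The battery after module 8 may be kept as an additional measurement for completers.

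The cost is a platform scheduling change, some extra reminders and calls, and a short protocol amendment. Fast finishers will either wait for the battery or complete it twice. If non-completers are already assessed in this way in practice, one sentence saying so, with the timing and the origin of the follow-up dates, resolves the point.
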